### Intervention and further activity outcomes

Compliance and adherence to the trainings and the reasons for not attending or aborting a training session are recorded during the intervention period (T0–T1, see Table 2, Figs. 1 and 3). Additionally, participants in the intervention group are asked to rate the motor-cognitive task difficulty of the training tasks (perceived task difficulty, PTD) and their motor-cognitive performance (perceived performance, PP) in every training session (during T0–T1, see Table 2, Figs. 1 and 3). Visual analogue scales (VAS) in the eCRF based on the cognitive load theory [130] and the NASA-TLX [National Aeronautics and Space Administration Task Load Index [131]] are used to collect these ratings (Additional file 1). PTD and PP are expressed as percentage values where higher percentages stand for more difficult tasks and better performance, respectively. The intervention outcomes are summarised in Table 4.

All participants are interviewed weekly throughout the whole study (T0–T2, see Table 2, Figs. 1 and 3) regarding the dose (frequency and time) and content (intensity and type) of moderate to intense physical and cognitive activities, which they perform as part of their usual care or in their leisure time. Definitions for moderate to intense activities are based on the World Health Organisation’s (WHO) 2020 Guidelines on Physical Activity and Sedentary Behaviour [132]. The interviews are done using a structured questionnaire (Additional file 1), which implies the FITT-VP principles [70] and the TIDieR checklist [Template for Intervention Description and Replication [133]]. The further activity outcomes are summarised in Table 4.

## Participant timeline {13}

Each participant is involved for approximately 24 weeks (12 weeks intervention period, 12 weeks follow-up period, Figs. 1 and 3). Participants are contacted and screened for eligibility by their therapist, physician, and/or the study team. Eligible, potential participants are provided with detailed study information in oral and written form. Interested potential participants are invited to a first study appointment, where they are first again provided with the study information, especially outlining the benefits, risks, and their rights associated with the study, and can clarify remaining questions. Trained movement scientists and therapists then obtain written informed consent from those willing and able to participate in the study, before any study-related procedures start. After that, participants first attend the baseline measurement (T0, Figs. 1 and 3). Subsequently, the participant is allocated randomly to one of the two study arms. Randomisation for each participant is run in Research Electronic Data Capture (REDCap) by an investigator other than the blinded assessor. Participants allocated to the intervention group thereafter attend concept-guided, personalised motor-cognitive training, twice a week for 12 weeks (T0–T1). Participants allocated to the control group receive no additional intervention during the same 12 weeks (T0–T1). After completion of the intervention period, all participants attend the post-intervention measurement (T1, Figs. 1 and 3). During the subsequent 12-week follow-up period (T1-T2), participants in both groups receive no additional intervention. At the end of this period, all participants attend the follow-up measurement (T2).

## Sample size {14}

A sample size of 38 participants (approx. 19 per group) was estimated for this study. The sample size estimation was based on systematic reviews investigating the effects of motor-cognitive training and exergames on cognitive functions. Stanmore et al. included studies with any population (including five out of seventeen studies with stroke or other neurological patients) and found a small to medium effect for global cognitive functioning (SMD = 0.44, *p* = 0.001) and several small to large effects for cognitive domains including executive functions, processing speed and visuospatial skills (0.26 ≤ SMD ≤ 0.90, *p* < 0.05) (132). Five further reviews included studies with older adults and found small to large effect sizes for global or overall cognitive functioning and cognitive domains including attention, executive functions, learning and memory, and processing speed (0.30 ≤ SMD ≤ 1.37, *p* < 0.05) [31, 35, 54, 56, 134]. Based on this evidence, a small to medium effect on global cognitive functioning is anticipated for the planned study (*f* = 0.21). The sample size was estimated using G*Power, entering this effect size (requiring no expected difference between groups and standard deviations) and the following parameters into the mask for a two-way mixed ANOVA; α-level = 0.05, power = 0.80, number of groups = 2, number of measurements = 3, correlation among rep measures = 0.5, nonsphericity correction = 1. Dropouts will be replaced by post-recruitment until the planned sample size is achieved. Based on the recent feasibility study [85] and comparable literature [135–137], a dropout rate of 10–20% can be expected.

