Due to its design, this study will have two major limitations. (1) Study participants will train 840 min with 100% adherence rate, which is at the lower border of recommended training volume for improving cognitive functions in chronic stroke and older adults [23, 27, 163, 164]. Similarly, some authors recommend more than two and longer sessions per week [55, 164]. However, practical reasons including that participants needed to come into the study centre twice a week limited more training time in this study. Moreover, the feasibility study preceding this RCT showed that participants preferred two sessions per week, lasting 30 to 40 min and no longer [85]. To prevent over-request of time expenditure of the participants and, thereby, harm recruitment, the total training volume was kept at this lower border of recommended time. (2) The black box of usual care and leisure time physical and cognitive activities may influence the measured outcomes as well. Usual care is a wide term and has been reported to include a wide range of interventions, doses, intensities, and implementations [165, 166]. This limitation is addressed by recording the participants’ usual care and general activities besides the study intervention and by considering this in the analysis. (3) This study’s sample size was not based on a standard RCT sample size calculation, as at the time of planning, no expected values for difference between groups and standard deviations for the MoCA in chronic stroke were available due to the novelty of the topic in research. Therefore, the sample size was estimated based on effect sizes from systematic reviews in related literature (see the ‘Sample size’ section).

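### The effect size behind the 38 participants (f = 0.21) means a group difference of about 0.89 SD in the calculation that yields 38, not the small to medium effect the text anticipates; at the plan's correlation of 0.5, power for the cited SMD of 0.44 is about 26% to 46%, depending on the analysis.

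*Protocol article*

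**What the plan says.** All the inputs are in the protocol article under Sample size {14}:

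- The target: "A sample size of 38 participants (approx. 19 per group) was estimated for this study".
- The evidence on the primary construct: one review "found a small to medium effect for global cognitive functioning (SMD = 0.44, *p* = 0.001". For cognitive domains the same review gives SMDs of 0.26 to 0.90. Five further reviews in older adults give 0.30 to 1.37 across global cognition and domains.
- The planning effect: "a small to medium effect on global cognitive functioning is anticipated for the planned study", with f = 0.21.
- The settings: "α-level = 0.05, power = 0.80", then "number of groups = 2, number of measurements = 3, correlation among rep measures = 0.5, nonsphericity correction = 1", in the G*Power mask for a two-way mixed ANOVA.

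The section gives no conversion from SMD to f and does not say whether the between, within or interaction effect was tested. Under Statistical methods {20a}, the treatment effect is carried by the group-by-time terms at T1 and T2. In the Discussion, limitation (3) concedes that this was not a standard RCT calculation, because no MoCA group difference or SD was available, and says that "the sample size was estimated based on effect sizes from systematic reviews in related literature".

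**The concern.** Cohen's f is not on one scale across the options of a repeated-measures ANOVA. For a between-group factor with two equal groups, f is half the standardised group difference. For a group-by-time interaction, f is the standard deviation of the interaction components of the cell means, divided by the outcome SD. A given group difference therefore becomes a much smaller f. An f of 0.21 looks small to medium on the first scale but represents a large treatment difference on the second.

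This is the only power statement for the primary outcome. If the value was used on the interaction scale, the text and the calculation describe different effects. A reader would credit the trial with 80% power for an effect that it is unlikely to detect, and could take a non-significant MoCA result as evidence against a benefit of the size cited.

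**Working it through.** **Inputs from the plan:** N = 38 (19 per group), alpha 0.05, target power 0.80, f = 0.21, k = 2 groups, m = 3 measurements, rho = 0.5, nonsphericity correction 1, cited SMD 0.44.

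**1. Reproduce the plan's figure.**

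- Group-by-time interaction: lambda = f² × N × m / (1 − rho) = 0.0441 × 38 × 3 / 0.5 = 10.05, with df 2 and 72. Power is 0.8003. At N = 36 it is 0.776, so 38 is the smallest even N.
- Within factor (time): the same lambda and df for two groups, so it also returns 38. It tests change over time and no treatment effect.
- Between factor: lambda = f² × N × m / (1 + (m − 1) × rho). Power at N = 38 is 0.34, and 80% needs 122.

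The interaction is therefore the option that both yields 38 and tests treatment, in line with the planned model.

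**2. Translate f = 0.21 into a group difference.** Let the standardised difference be 0 at T0 (randomised groups) and d at T1 and T2.

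- Mean difference over visits: 2d/3. Deviations: −2d/3, d/3, d/3.
- Each group carries half of each deviation, so f² = (1/3) × (1/4) × (4/9 + 1/9 + 1/9) × d² = d²/18, and f = 0.2357d.
- d = 0.21 / 0.2357 = 0.89.

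A difference at T1 only gives the same 0.89. If the effect halves by T2, f = 0.21 means d = 1.03.

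**3. Power for SMD 0.44 at N = 38, rho = 0.5.** f = 0.2357 × 0.44 = 0.104; lambda = (0.44²/18) × 38 × 3 / 0.5 = 2.45; power 0.259. Reaching 80% on this test would need N = 152. Single contrasts at 19 per group use noncentrality (0.44/s) × √(19/2), where s² is the variance of the contrast in units of the outcome variance:

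| Analysis | s² at rho = 0.5 | Power |
|---|---|---|
| Omnibus interaction | – | 26% |
| Change score T1 − T0 | 2(1 − rho) = 1 | 26% |
| Baseline-adjusted, T1 | 1 − rho² = 0.75 | 33% |
| Baseline-adjusted, mean of T1 and T2 | (1 + rho)/2 − rho² = 0.50 | 46% |

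If the effect halves by T2, omnibus power is 20%.

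**4. Sensitivity to the correlation.** The document gives no observed MoCA correlation; 0.5 is its planning value, and the others below are assumptions.

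| rho | 0.5 | 0.6 | 0.7 | 0.8 | 0.9 |
|---|---|---|---|---|---|
| Omnibus power, SMD 0.44 | 26% | 32% | 41% | 57% | 88% |

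**5. What 38 participants detect with 80% power at rho = 0.5.** About 0.89 SD in the omnibus interaction. For a change score at T1, about 0.93 SD; for a baseline-adjusted T1 contrast, about 0.93 × √0.75 = 0.81 SD.

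**6. On the MoCA scale.** If the SD were 2.5 to 4 points (an assumption; the document gives none), 0.89 SD would be 0.89 × 2.5 = 2.2 to 0.89 × 4 = 3.6 points, against the 1.22 points the plan treats as clinically relevant.

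**The case against.** Several points on the other side are fair.

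- **The arithmetic is right.** With the listed inputs, f = 0.21 gives 80% power at 38. The plan never claims 80% power for an SMD of 0.44. This stands: the fault lies in the meaning of the effect size, not in the computation.
- **The conversion is not documented.** A reader might infer that f was obtained as half the SMD. The document does not say so: 0.44/2 is 0.22, which would have needed only 36 participants (power 0.815). Halving is a plausible origin and no more. The point does not depend on it, because 0.21 means about 0.89 SD in the interaction option however it arose.
- **The tested effect is not named.** A reader might also say that only the interaction option yields 38. That is too strong, since the within-factor option does too. The interaction reading rests on the planned model.
- **Larger effects are cited.** The ranges reach 0.90 and 1.37, and 0.89 lies inside both. But they include individual domains and, in five reviews, older adults. The plan's own label is small to medium, the one it gives to 0.44.
- **Limitation (3) warns the reader.** It admits a weak basis. It still presents the size as resting on the reviews and does not disclose the difference in scale. No MoCA SD is needed to see that difference.
- **The correlation may be higher and the analysis more efficient.** True, so the power has to be given as a conditional range.

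**Conclusion.** The point holds. The plan anticipates a small to medium effect on global cognition, but the calculation that produces 38 is powered at 80% for about 0.89 SD at T1 and T2, roughly twice the cited 0.44. At the plan's own correlation of 0.5, power for 0.44 is about 26% to 46%, depending on the analysis.

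This rests on four assumptions: the group-by-time option was the one used; the groups do not differ at T0; the difference is equal at T1 and T2; and the SMD is standardised by the outcome SD. The flat reading that power is 26% is not supported without the conditions attached: it requires rho = 0.5 and no baseline adjustment. For the omnibus test, 80% would be passed only somewhere between rho 0.8 (57%) and 0.9 (88%). Nor do the documents say that a null result would be presented as adequately powered; that is a risk of the present wording.

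**What to change.** In the sample-size paragraph, name the tested effect and the meaning of f. State that, at rho = 0.5, 38 participants give 80% power for a group difference of about 0.89 SD at T1 and T2 (about 0.81 SD for a baseline-adjusted T1 contrast), and about 26% to 46% power for an SMD of 0.44, depending on the analysis. Remove the implication that a small to medium effect is powered at 80%. Put the same disclosure in limitation (3).

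Secondarily, add that a non-significant MoCA result will be interpreted through the 95% confidence interval for the group difference against 1.22 points. At present, Methods for additional analysis {20b} compares differences with that threshold only for outcomes that reach significance.

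The cost is rewording and a less favourable power statement. With 37 participants already retained at submission, no extra recruitment and no change to procedures is asked for.

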## Recruitment {15}

The PEMOCS study is a single-blind randomised control trial (RCT) with chronic stroke survivors recruited from hospitals and rehabilitation centres in the Canton of Zurich, Switzerland. Participants are recruited by therapists and physicians during therapy sessions and stroke follow-up appointments, by flyers on the ward, and by contact of the study team in case of provided general consent. Regular contact between the recruiters and study team meetings should help to maintain an acceptable recruitment rate.

## Assignment of interventions: allocation

### Sequence generation {16a}, concealment mechanism {16b}, and implementation {16c}

The randomisation is stratified by cognitive status (cognitive impairment absent or present, determined by a MoCA score ≥ 24 or < 24, respectively [74, 100, 101]) and by sex (female or male [138–140]). Both stratifying variables are allocated 1:1 to both groups. Participants are randomised using REDCap, the same tool as utilised for eCRF keeping (see the ‘Data management’ section [141, 142]). To perform the randomisation in REDCap, a pre-defined randomisation list in the form of an excel document needs to be uploaded onto the platform, which is then being used by the software. Instructions by REDCap show how this list must be structured to provide the desired allocation ratio and stratification [141, 142]. These instructions were followed by the randomisation-list creator, a person otherwise not involved in the study. This way it was ensured that no member of the study team would know the allocation sequence. After creating the list, the randomisation-list creator encrypted the excel document containing the list with a password. Both, the list and the password, are stored in a secure place, where the investigators of the study team have no access. Moreover, the REDCap user rights to access and view the randomisation setup feature were removed from all investigators of the study team before the final randomisation list was uploaded onto the REDCap platform [141, 142].

Study investigators other than the blinded assessor enrol participants and allocate them to groups. A separate instrument in REDCap, which is invisible for the assessor through user privileges, is used for randomisation.

## Assignment of interventions: blinding

### Who will be blinded {17a}

Outcome assessors are blinded to group allocation. They cannot access the randomisation tool in REDCap and are not involved in intervention procedures. To blind the data analyst, a de-identified dataset will be used for analysis, which will not contain unique identifiers such as the study ID.

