### Trial design {8}

This study is a randomised, controlled trial (RCT) with two parallel arms, investigating the superiority of a concept-guided, personalised, motor-cognitive exergame training added to usual care over usual care alone. The trial employs a single-blinded approach, with outcome assessors being unaware of group assignments. The randomisation is performed with a 1:1 ratio using stratification by sex (female or male [73]) and cognitive impairment (MoCA ≥ 24 or MoCA < 24 [74]).

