## Outcomes {12}

Primary and secondary outcomes are collected at three time points (T0–week 0, T1–week 12, T2–week 24; see Table 2, Figs. 1 and 3) by cognitive and motor assessments as well as a health-related-quality-of-life questionnaire. At the baseline measurement (T0), participant characteristics and baseline factors are recorded. Intervention and activity outcomes are collected during the intervention (T0–T1) and the follow-up (T1–T2) periods, respectively. All variables will be aggregated as means or medians, depending on the distribution of the data, and the analysis metric for all will be final values (see the ‘ Statistical methods’ section). An overview of all outcome variables is presented in Tables 3 and 4.

**Table 2 Tab2:** Overview over outcome recording. *ADH*, adherence; *BBS*, Berg Balance Scale; *BQ*, baseline questionnaire, incl. see the ‘ Baseline factors’ section; *TUG(-Cogn)*, (cognitive dual-task) Timed Up and Go test; *CPL*, compliance; *FAC*, Functional Ambulation Category; *FM-LE*, lower-extremity component of Fugl-Meyer assessment; *MoCA*, Montreal Cognitive Assessment; *mRS*, modified Rankin scale; *MRT*, mental rotation test; *NBT*, N-back test; *NIHSS*, National Institute of Health Stroke Scale; *OWA*, outdoor walking assessment; *PCA*, physical and cognitive activities; *PP*, perceived performance; *PTD*, perceived task difficulty; *SIS 3.0*, Stroke Impact Scale; *SRT*, simple reaction test; *Stroop*, Stroop Interference test; *TMT*, Trail Making test; *UC*, usual care; *10MWT*, 10-m walk test

Time (weeks)	0	+ 1–12	+ 12	+ 13–24	+ 24
**Time point**	Baseline (T0)	Intervention period	Post-intervention (T1)	Follow-up period	Follow-up (T2)
**Study staff**	Assessor	Training supervisor	Blinded assessor	Training supervisor	Blinded assessor
**Baseline factors:** BQ, NIHSS, FAC, mRS, BBS, FM-LE	+				
**1° Endpoint:** MoCA	+		+		+
**2° Endpoints:** SIS 3.0, SRT, TMT, Stroop, NBT, MRT, TUG(-Cogn), 10MWT, OWA	+		+		+
**Intervention Endpoints:** CPL, ADH, PTD, PP		+ *(intervention group only)*			
**Activity Endpoints:** UC, PCA		+		+

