### Procedure for unblinding if needed {17b}

N/A, as assessors, who are the only blinded members of the study team, are always accompanied by a training supervisor, who knows the participants and their group allocation. Hence, in case any situation during a measurement session would require knowledge of group allocation, the training supervisor can handle it and the assessor does not need to be unblinded.

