### Data management {19}

An electronic case report form (eCRF) is kept for each enrolled participant using REDCap electronic data capture tools hosted at ETH Zurich [141, 142]. REDCap (Research Electronic Data Capture) is a secure, web-based software platform designed to support data capture for research studies, providing (1) an intuitive interface for validated data capture, (2) audit trails for tracking data manipulation and export procedures, (3) automated export procedures for seamless data downloads to common statistical packages, and (4) procedures for data integration and interoperability with external sources [141, 142]. This eCRF has been validated before enrolment of the first participant. Study team members who are authorised to enter or edit data in the eCRFs, receive a login to the REDCap study platform, and are listed with signatures in the trial master file (TMF) and the investigator site file (ISF). To assure that any authorised person, who may perform data entries and changes in the eCRF, can be identified, all entries/edits are recorded with name, date, and time. Data entry of the primary and secondary outcomes in REDCap is performed by one and double-checked by another investigator (verification, four-eyes-principle). Should any previously entered data need to be changed (e.g. because a mistake was identified during the verification), a reason must be given to proceed. eCRFs are kept current to reflect participant status at each phase during the study.

Study and participant data will be handled with uttermost discretion and are only accessible to authorised personnel who require the data to fulfil their duties within the scope of the study. Participants are coded and not identifiable in the eCRF or on any other study-specific documents. Appropriate coded identification (study ID) is used. Each study ID composes of four random letters or numbers, which are not related to any characteristics, or the time point of inclusion of the participants. The sponsor will store the participant identification list in a secured and locked location. All study data are archived for ten years after study termination or premature termination of the study.

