Assumptions on the residuals of primary and secondary outcomes will be checked using the DHARMa package in R [147]. Appropriate actions will be taken if one or more assumptions are not met. All primary and secondary outcomes will be analysed following the standard intention-to-treat (ITT [148, 149]) principle using linear mixed-effects models (LMEM, lme4 package in R). Subject-specific random intercepts will account for within-subject correlations between time points. Follow-up scores (T2) of the outcomes will be the dependent variables of the models, while group (intervention vs. control, control being the reference), time (T0, T1, T2), and group x time interactions at T1 and at T2, respectively, will be included as independent variables (fixed effects). Baseline factors such as age, sex, and time since stroke will be considered as covariates. Missing data of whole measurement time points (i.e. of dropouts) will be accounted for with the ‘last observation carried forward’ method. For single missing data points (e.g. if a participant did not perform an assessment at one time point or a technical issue produced missing data at one time point), however, no data imputation will be performed as LMEMs can be fitted even if some outcome data are missing [145, 150]. For the outdoor walking assessment (OWA), high occurrence of missing data is expected, as ability to walk 400 m is not covered by the eligibility criteria and varying weather conditions on the measurement days may interfere with the assessment. Therefore, for the OWA outcome parameters, datasets of participants who did not perform the OWA at one or several time points will be excluded from the analysis. Significance will be set to *p* < 0.05. Effect sizes will be calculated as *r* (Bravais-Person correlation coefficient) and interpreted as small (*r* < 0.3), medium (*r* < 0.5), and large (*r* ≥ 0.5) [145].

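### Removing the study ID does not mask the treatment arm, so the stated method does not achieve the claimed blinding of the data analyst

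*Protocol article*

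**What the plan says.** Five places in the protocol article bear on this.

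- **Who will be blinded {17a}** names assessors and then the analyst, and gives the method for the analyst: "To blind the data analyst, a de-identified dataset will be used for analysis, which will not contain unique identifiers such as the study ID".
- **The section on unblinding {17b}** rests on "assessors, who are the only blinded members of the study team". **Trial design {8}** says: "The trial employs a single-blinded approach, with outcome assessors being unaware of group assignments". It does not mention the analyst.
- **Data management {19}** describes the identifier: "Each study ID composes of four random letters or numbers, which are not related to any characteristics".
- **Statistical methods {20a}** has as a fixed effect "group (intervention vs. control, control being the reference". It leaves the choice among baseline covariates open and says of the residual checks: "Appropriate actions will be taken if one or more assumptions are not met".
- **Outcomes {12}, Table 2** marks compliance, adherence, perceived task difficulty and perceived performance as "intervention group only". The additional-analysis section {20b} then uses an adherence rate of at least 85% to define the per-protocol set.

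**The concern.** De-identification and masking of allocation protect against different things. The first hides who a participant is; the second hides which treatment the participant received. The article claims the second and describes only the first.

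Analyst blinding matters most where the analysis still contains choices, and here it does. Age, sex, time since stroke and the volumes of usual care and activities are candidate covariates without a fixed list, and the response to a failed assumption is not named. An analyst who can see the arms makes these choices knowing which direction favours the intervention. The trial report could nevertheless describe the analysis as blinded on the strength of {17a}.

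**Working it through.** The plan gives no figure for this point and no arithmetic applies. The check sets the sections side by side.

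1. **What does deleting the ID remove?** By {19} the ID is random and unrelated to participant characteristics. It does not encode the arm, so a row without it says as much about allocation as a row with it. What is lost is the link from the row to a known person. That helps if the analyst has met participants and remembers their allocation, and only then.

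2. **Is the arm otherwise hidden?** The model in {20a} needs a group variable. The article does not say that this variable is delivered under neutral labels, or who would hold the code.

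3. **Would neutral labels be enough?** Not if the file also holds the variables that Table 2 restricts to the intervention arm: whichever coded arm has adherence values is the intervention arm. The per-protocol flag carries similar information. A participant who stayed through the intervention period but is excluded for adherence below 85% can only have been in the intervention arm.

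4. **Can the primary analysis be run without those variables?** Yes. The section on intervention and activity outcomes reports compliance, adherence and the two ratings descriptively. The covariates it offers for the models are the volumes of usual care and activities, which Table 2 records in both arms. Adherence is needed only for the per-protocol repeat.

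5. **Can the model be fitted to arms labelled A and B?** Yes. Replacing the group indicator G by 1 − G in a model with group, time and their interaction reverses the sign of the group-by-time coefficients. It leaves their standard errors and two-sided p-values unchanged. Masking therefore costs nothing analytically.

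6. **Do {17a} and {17b} agree?** {17a} sets out to blind the analyst. {17b} limits blinding within the study team to assessors. Both can be true only if the analyst is not a member of the team. The article does not say who the analyst is. The section on the coordinating centre {5d} gives everything except recruitment and screening to the sponsor/principal investigator team, which makes an outside analyst less likely but does not exclude one.

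**The case against.** The strongest reply is that this is a condensed article. Coding of arm labels may be described in the full protocol or the analysis plan, and removing the ID serves a real purpose. The trial also calls itself single-blind on the basis of its assessors, and no design step depends on a blinded analyst. Part of this stands: masked labels may well be used in practice, and the consequence is limited. But the article did not leave the method to another document. It named one, and that method does not do what is claimed for it.

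Several stronger readings are tempting but not supported:

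- **That analyst blinding does not exist.** The text shows only that the stated method does not produce it. Naming control as the reference defines the contrast, not the labels in the analyst's file.
- **That {17a} and {17b} flatly contradict each other.** {17b} concerns unblinding during a measurement session and speaks of the study team. The conflict depends on the analyst belonging to that team.
- **That the intervention-only variables must unmask the primary analysis.** Nothing says they are in the primary file.
- **That removing identifiers leaves no grouping key for the random intercept.** An arbitrary row key is compatible with {17a}.
- **That the choice of software adds freedom to the main model.** R or SPSS is named in general, but {20a} fixes the mixed models to lme4 and the residual checks to DHARMa, both in R.
- **That the defect inflates the type I error by a calculable amount.** By step 5, two-sided p-values are the same under A/B labels. A search over covariate sets would therefore yield a result below 0.05 equally often with masked arms. Such a rate would measure the open covariate list, not the lack of masking. Masking affects only whether the analyst knows which direction is favourable.

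**Conclusion.** The point holds in this form: {17a} claims a blinded analyst by a mechanism that does not mask the arm. {17b} is inconsistent with {17a} unless the analyst is outside the study team, which is not stated. The first part rests on the text alone and stands whoever the analyst is; the second is conditional on team membership.

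No magnitude is claimed. The blinding of assessors, which protects the measurement of the primary outcome, is not affected. What is at stake is whether the report may call its analysis blinded while covariate selection and assumption remedies remain open. It should be corrected, but it is not a threat to the design.

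**What to change.** In {17a}, choose one of two courses.

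- **Mask the arm.** State that a person independent of the analysis prepares the file with a neutral subject key and arms coded A/B; the randomisation-list creator, described as otherwise uninvolved, is one candidate. Withhold compliance, adherence, both perceived ratings and the per-protocol flag. Release the code and these variables only after the primary intention-to-treat model, its covariates and its assumption remedies are locked.
- **Or drop the claim.** Delete the sentence on blinding the analyst and keep the description of a single-blind trial with blinded assessors.

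Then align {8} and {17b} with the choice, and say whether the analyst belongs to the study team.

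The cost of the first course is one recoding step, a few sentences, and a short delay before the per-protocol analysis and the intervention descriptives can start. Trial conduct is not touched: the trial status section describes the study as still running, so the file can be prepared this way before analysis. The second course costs only the edit.
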